| Statistical Rationale       | 
Efficacy:
 
The efficacy of the experimental intervention will be determined by testing and estimating differences regarding the absolute change in SARA total score measured at the 2-week visit and at the end of the verum/ placebo period compared to period-level baseline at visit 2 (treatment period 1) and at visit 5 (treatment period 2)
 
Description of the primary efficacy and population:
 
To analyze the differences in SARA total score between both treatments, a linear mixed effects model for DeltaSARA for the absolute change in SARA total score will be performed (fixed effects: factors for treatment visit, treatment-by-visit interaction, mean of both period-level baseline SARA total scores as covariate; patient-specific random intercepts).
 
The primary efficacy analysis will be performed according to the intention-to-treat (ITT) principle. Sensitivity analyses to assess robustness of trial results include multiple imputation techniques for the missing primary outcome. The significance level is <math>\alpha = 5\%</math>.
 
Safety:
 
Data about adverse events will be descriptively analyzed by verum and placebo phase.
 
Secondary endpoints:
 
The confirmatory analysis extends to the key secondary endpoint EQ-5D-5L if a benefit in the primary analysis could be demonstrated. Then this analysis will also be based on the ITT principle. Further secondary endpoints are the subscores of SARA and SCAFI, BDI-II, and FSS, which are not considered in the hierarchical multiple testing procedures and therefore will be analyzed descriptively (mainly by the Wilcoxon signed rank test where considered appropriate). The corresponding confidence intervals for treatment group effects will be reported. Change scores will be assessed at the 6-week visit at the end of the verum/ placebo
 |

Confidential

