## 13 Statistical Methods

### 13.1 Planned Statistical Analyses

#### **Analysis of primary endpoint:**

For the primary outcome change in SARA total score (DeltaSARA), the null hypothesis will be tested that the mean change is the same on placebo and on acetyl-DL-leucine. The significance level alpha is set to 5%.

The primary efficacy analysis will be performed according to the intention-to-treat (ITT) principle. Absolute change calculated as the difference between the period-level baseline score and the score measured at the 2-week visit and at the 6-week visit of the verum/ placebo period will be considered for a model-based primary efficacy analysis. If not revised in the *statistical analysis plan* (SAP), a linear mixed effects model for DeltaSARA will be performed (fixed effects: factors for treatment and visit, treatment-by-visit interaction, mean of both period-level baseline SARA total scores as covariate; normally distributed patient-specific random intercepts) in order to deal with repeated measurements within periods and measurements not made at equivalent times on each subject (due to unscheduled or missed clinic visits). This subject-specific modelling approach allows individual change scores over time to be calculated. To analyse the differences between both treatments at the end of the 6-week treatment period, 95% confidence intervals will be provided to quantitatively describe treatment effects.

Sensitivity analyses will be performed on a per protocol approach which accounts for compliance with medication according to the protocol. Additional efficacy analyses adjusting for genetically vs. sporadic CA, gender, age, or trial site, will be performed. Besides, the robustness of the overall result will be investigated by sensitivity analyses adjusting for speech-/physiotherapy (as considered appropriate during the blinded data review depending on the data quality). Further methodological details will be provided in the SAP.

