### 13.3 Sample Size Calculation

The sample size was calculated on the basis of the primary hypothesis, using own preliminary case series data (n=13 patients; [10]) and a similar placebo-controlled trial (N=20 patients; [31]) evaluating the efficacy of varenicline on the improvement in SARA total score in patients with SCA3.

Hence, assuming a minimum clinically relevant improvement in the SARA total score of 1.5 points [28] (the absolute change under verum is by 1.5 score points better as the change under placebo) and a standard deviation of the individual SARA change of 3.0 (which results in a standard deviation of 4.2 assuming an intra-patient correlation of 0.6), a **sample size of 86** (85 is calculated but 2 sequences are needed) **in total** is needed to have 90% power to detect a difference in means of 1.5, using a paired t-test with a 0.05 two-sided significance level [Software used: nQuery Advisor 7.0].

Assuming a dropout rate of about 20%, **a total of 108 patients have to be allocated to the trial**. With a proportion of about 50-55% recruited patients out of the number to be screened, 200 patients have to be assessed for eligibility.

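### The default primary model has a patient random intercept as its only stated random term, although both changes in a period share one baseline, so the week-6 standard error is too small

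*Protocol*

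**What the plan says.** Section 13.1 defines the outcome of the primary model as "the difference between the period-level baseline score and the score measured at the 2-week visit and at the 6-week visit" of each period. A patient who completes the trial therefore contributes four changes. The period baselines are the scores at visit 2 and visit 5 (synopsis, Trial Endpoints).

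The fixed effects are treatment, visit, their interaction and the mean of the two period baselines. The random part is "normally distributed patient-specific random intercepts) in order to deal with repeated measurements within periods". The synopsis (Statistical Rationale) gives the same structure: "mean of both period-level baseline SARA total scores as covariate; patient-specific random intercepts". Neither place names a patient-by-period term, a residual covariance structure or a robust standard error.

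Section 13.1 allows the SAP to revise the model; the synopsis carries no such caveat. The primary endpoint is the change to the end of the 6-week period (6.2), and 13.1 directs the treatment comparison to that time. On the error level, 13.1 states "The significance level alpha is set to 5" (percent), and 13.3 makes it two-sided.

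**The concern.** Section 13.1 presents the patient intercept as the device that handles repeated measurements within a period, but the intercept contains nothing specific to a period. Measurement error in the visit 2 score enters both period 1 changes and neither period 2 change; the visit 5 score does the same for period 2. The covariate cannot absorb this, because a mean of both baselines is one constant per patient.

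Treatment is compared between periods, so the omitted patient-by-period variation is exactly the variation that the treatment contrast carries. The model pools it with visit-to-visit noise and in effect counts week 2 and week 6 as more separate evidence than they are.

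The error level of the trial's confirmatory test is at stake. That test also opens the confirmatory testing of EQ-5D-5L, so any excess error passes down the hierarchy. The listed sensitivity analyses (per protocol, covariate adjustment, imputation) leave the covariance structure alone and would not reveal the fault.

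**Working it through.** **The plan's own figure.** Section 13.3 says the sample "is needed to have 90% power to detect a difference in means of 1.5, using a paired t-test with a 0.05 two-sided significance level". It assumes "a standard deviation of the individual SARA change of 3.0", "which results in a standard deviation of 4.2 assuming an intra-patient correlation of 0.6". An exact paired t-test calculation with difference 1.5 and SD 4.2 gives n = 85, which is rounded to 86 (power 90.6%). With 20% dropout, 86/0.8 = 107.5, hence 108. Both figures reproduce. The planning test compares one value per period, so it does not have the fault described here.

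**Which cross-period correlation applies.** SD 4.2 is about 3.0 × √2 = 4.24, which corresponds to correlation 0, while the text states 0.6. That mismatch is a separate matter, but it leaves the cross-period correlation unclear, so both values are tried below.

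**Notation.** Let e² be the visit variance and g² the patient-by-period variance of the changes.

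- True variance of the week-6 contrast: 2(e² + g²)/n.
- Each patient has three within-patient degrees of freedom: one between periods, with expected mean square e² + 2g², and two within periods, with e² each. The fitted model pools them: (3e² + 2g²)/3 = e² + (2/3)g².
- Variance the model reports: 2(e² + (2/3)g²)/n.

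Let rw be the correlation of the two changes within a period and rc the correlation across periods. The ratio of reported to true variance is then R = [1 − (rw + 2rc)/3]/(1 − rc), and the actual two-sided level is 2[1 − Φ(1.96√R)]. The level is 5% only if rw = rc.

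**Reference case: equal, independent noise at baseline, week 2 and week 6.** Here g² = e², or rw = rc + (1 − rc)/2. With SD of change 3.0 and rc = 0, e² = g² = 4.5.

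- True SE: √(2 × 9/86) = 0.4575.
- Reported SE: √(2 × 7.5/86) = 0.4176.
- Ratio: 0.913, so the SE is about 9% too small.
- Level: 2[1 − Φ(1.789)] = 7.4%, so a nominal 95% interval covers about 92.6%.

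The ratio is the same for any rc in this case.

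**Other correlations, week-6 contrast**

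| rc | rw | SE ratio | Actual level |
|---|---|---|---|
| 0.6 | 0.7 | 0.957 | 6.1% |
| 0 | 0.3 | 0.949 | 6.3% |
| 0 | 0.5 | 0.913 | 7.4% |
| 0.6 | 0.8 | 0.913 | 7.4% |
| 0 | 0.7 | 0.876 | 8.6% |
| 0.6 | 0.9 | 0.866 | 9.0% |

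**Simulation under the null, n = 86.** With 40,000 replicates per scenario, the reference case rejected in 7.3 to 7.6% of trials, and serially correlated scores gave 8.9 to 10.8%. Analyses with a correct covariance held 4.9 to 5.2%. Direct REML fits of the stated model (250 data sets) gave a mean reported SE of 0.417, in line with the formula.

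**Period effect.** The model has no period term. A period difference of d points adds about d²/3 to the pooled residual and so raises the reported SE. With e² = g² = 4.5 and d = 1, R = (7.5 + 0.333)/9 = 0.870 and the level is about 6.7%; a separate simulation with a 1-point period effect gave 6.4%. This offsets the inflation only in part.

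**The case against.** The strongest defence is that the model is provisional. Section 13.1 lets the SAP revise it and promises further detail there, and residual covariance is often settled in a SAP. Moreover, the text never says the residuals are independent, so a patient intercept combined with a structured residual covariance would fit the wording. Part of this stands: the inflation is conditional on the usual independent residuals, and the SAP is a legitimate place to repair it. It does not remove the point. The protocol does not leave the random structure open. It states one, says that it handles the repeated measurements within periods, and repeats it in the synopsis without the caveat. If nobody revises it, that model is the one that will be fitted.

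The second objection concerns size, and it stands. The protocol gives no within-period correlation, so every figure above rests on an assumption.

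Because the synopsis also mentions the 2-week visit, a reader might infer that the primary test is of a treatment effect averaged over both visits, for which the inflation would be considerably larger. The documents do not support that reading. Section 6.2 defines the endpoint as the 6-week change, 13.1 places the treatment comparison at week 6, and no visit-averaged effect is defined anywhere as the primary estimate. Nor does anything in the protocol support the extreme case in which patient-by-period variance swamps visit noise.

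**Conclusion.** Wrong as written. Fitted as stated with independent residuals, the primary model understates the standard error of the week-6 contrast. The direction follows from the design: changes share a baseline within a period and not across periods, so rw exceeds rc unless the baseline is error-free and patients do not vary between periods.

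The size is moderate and depends on assumptions. With equal, independent visit noise, the SE is about 9% too small and the nominal 5% test runs at about 7.4%. Over plausible correlations the range is about 6 to 9%, somewhat higher with serially correlated scores and lower if there is a period effect. These figures assume complete data from 86 patients. The fault lies in the precision claimed for the treatment estimate; the estimate itself is not biased by it.

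**What to change.** In section 13.1 and the synopsis, add a patient-by-period random intercept to the patient intercept, or replace the random part with an unstructured covariance over the four changes. The revision route to the SAP that 13.1 provides would also serve, provided it is used before unblinding.

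In simulation, a correct covariance brings the level back to 4.9 to 5.2% at week 6. The sample size of 86 does not change on this account, because it rests on a paired t-test that already holds its level. The cost is one further model term and slightly wider intervals. If the protocol text itself is changed, the sponsor needs to judge under 18.5 whether that is a substantial amendment; revision through the SAP is the lighter route.

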#### **Analysis of key secondary endpoints:**

In case of a statistically significant primary efficacy result, confirmatory testing will be extended to the EQ-5D-5L (VAS and descriptive scale). Two-sided tests for detecting treatment differences will be carried out.

SCAFI (total score and 3 subscores), SARA subscale items, as well as patient-reported outcomes BDI-II and FSS are not considered in the hierarchical multiple testing procedures. Descriptive comparisons between treatment groups at the end of the 6-week verum/ placebo period will be performed by use of a two-sided Wilcoxon signed rank test, and additionally, Hodges-Lehmann estimation of the location shift between the two groups will be provided, as considered appropriate based on the blinded data. The same non-parametrical tests will be employed to estimate treatment differences at the follow-up visit 8 (close-out visit).

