| Trial Endpoints  | 
Primary efficacy endpoint:
 
SARA total score: absolute changes at the end of each treatment period compared to the period-level baseline defined as SARA score at visit 2 (treatment period 1) and at visit 5 (treatment period 2)
 
Key secondary endpoint(s):
 
SCAFI and subscores of SARA, QoL (EQ-5D-5L), depression (BDI-II), fatigue (FSS): absolute changes at the end of the 6-week treatment period compared to the period-level baseline defined as score at visit 2 (treatment period 1) and at visit 5 (treatment period 2).
 
Additionally, change scores at follow-up visit will be assessed.
 
Assessment of safety:
 
Documentation and reporting of side effects (AEs, SAEs, SUSARs)
 |

Confidential

|                           |                                                                                                                                                                                                                                                                                                                                                                                                                                                                                                                                                                                                                                                                                                                                                                                                                                                                                                                |

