| Trial Procedures | 
Before screening visit/visit 1:
 
 
• Written informed consent
 
 
Treatment period 1: visit 2, 3 and 4
 
Treatment period 2: visit 5, 6 and 7
 
Wash out period of 4 weeks: between visit 4 and 5
 
Follow up/ close-out: visit 8
 
Screening visit/visit 1
 
 
• Check of inclusion/exclusion criteria
 
• Blood test (clinical chemistry: sodium, potassium, creatinine, serum bilirubin level, AST, ALT, urea, ALP, TSH; blood count: hemoglobin, erythrocytes, hematocrit, thrombocytes, leukocytes)
 
• Pregnancy test for women of child bearing potential
 
• Documentation of adverse events
 
• Patient characteristics and medical history as well as medical history concerning the trial specific illness, including frequency of physiotherapy and speech therapy (documented in hours per week)
 
• Drug history including documentation of prior therapies/medications and concomitant medications for treatment of trial specific illness as well as drug history for other indications
 
• Documentation of concomitant medication
 
• Neurological examination
 
• Ataxia rating scale (SARA)
 
 |

Confidential

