### 6.4 Secondary Efficacy endpoint

Absolute changes in the

- subscores of SARA,
- SCAFI total score and subscores of SCAFI

as well as patient-reported outcomes

- EQ-5D-5L (visual analogue scale; descriptive system),
- Beck's Depression Inventory (BDI-II),
- and the Fatigue Severity Scale (FSS)

from (period-level) baseline to the 6-week visit at the end of the verum/ placebo treatment period. Additionally, change scores will be assessed at the follow-up visit 8.

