### 7.2 Intervention scheme

Study participants will be randomly assigned to one of two different treatment sequences, either Acetyl-DL-Leucine followed by placebo or vice versa.

Each sequence consists of a first 6 weeks (42 days) treatment period, a 4 weeks (28 days) wash-out period, a second 6 weeks (42 days) treatment period.

Finally, a post-treatment follow-up is scheduled 4 weeks (28 days) after the second treatment period (see Schedule of activities 2).

Figure 1 ALCAT trial: intervention scheme with study visits

[figure not shown]

\* Screening (visit 1) and visit 2 can take place at one time, when patients are native to medication.

If patients are on medication due to cerebellar ataxia (i.e. Acetyl-DL-Leucin, aminopyridine), there is a planned wash-out period of 4 weeks.

For the trial schedule please refer to *Schedule of Activities* (see section 2)

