**Confidential**

### 10.2.5 Follow-up period

The follow-up period takes place after treatment period 2 and lasts for 4 weeks. The follow up ends with visit 8 which is the final visit of the study. A delay of  $\pm 5$  days is acceptable.

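### Section 13.1 applies a paired test to treatment differences at visit 8, but visit 8 alone gives one value per patient after both treatments and so contains no verum–placebo pair

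*Protocol*

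**What the plan says.** The passages that bear on the point are all in the protocol.

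- **Design (section 7.2).** "Study participants will be randomly assigned to one of two different treatment sequences, either Acetyl-DL-Leucine followed by placebo or vice versa". Every patient is meant to receive both treatments.
- **Test at week 6 (section 13.1, key secondary endpoints).** For SCAFI, the SARA items, BDI-II and FSS, the comparison at the end of the 6-week periods "will be performed by use of a two-sided Wilcoxon signed rank test", with a Hodges-Lehmann estimate.
- **Test at visit 8 (same paragraph).** "The same non-parametrical tests will be employed to estimate treatment differences at the follow-up visit 8 (close-out visit".
- **Timing of visit 8.** Section 7.2: "a post-treatment follow-up is scheduled 4 weeks (28 days) after the second treatment period". Section 10.2.5: "The follow up ends with visit 8 which is the final visit of the study".
- **Visit 8 endpoint (section 6.4).** "Additionally, change scores will be assessed at the follow-up visit 8". Neither a reference visit nor a second value to pair it with is named.
- **Period baselines and wash-out (synopsis).** Change is taken from the "period-level baseline defined as score at visit 2 (treatment period 1) and at visit 5 (treatment period 2"), and the trial procedures give "Wash out period of 4 weeks: between visit 4 and 5". Visit 5 appears only as the baseline of period 2.

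**The concern.** A signed rank test needs two values per patient, or one within-patient difference. At week 6 these exist: visits 4 and 7 supply one value on verum and one on placebo. At visit 8 there is one value, taken after both treatments. An analyst who follows the sentence must either test something else under the same name or invent a pairing.

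Both substitutes that use visit 8 alone can mislead. A signed rank test of change to visit 8 asks whether patients changed over time. Section 5.2 of the protocol calls most cerebellar ataxias progressive, so zero change cannot be presumed. A comparison of the two sequences is a between-patient contrast in which first and last treatment differ together. Either result could be reported as a treatment difference at follow-up. The natural question for that visit, whether an effect outlasts treatment, would have no defined analysis.

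**Working it through.** The visit 8 sentence carries no figure of its own, so there is none to reproduce. The check has five steps.

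**1. Timing.** Section 2 gives V2 day 0, V4 day 42, V5 day 70, V7 day 112 and V8 day 140.
- V5 is 70 − 42 = 28 days after period 1.
- V8 is 140 − 112 = 28 days after period 2, and 140 − 42 = 98 days (14 weeks) after period 1.
- SARA, SCAFI and the questionnaires are scheduled at V2, V5 and V8.

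**2. Values per patient.**

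| Time point | On or after verum | On or after placebo | Pair? |
|---|---|---|---|
| Week 6 (V4, V7) | 1 | 1 | yes |
| Visit 8 alone | one value in total, after both | – | no |
| V5 and V8 together | 1 | 1 | yes, but the protocol does not define it |

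**3. What visit 8 alone estimates.** Assume a simple additive model.
- d5 and d8 are the mean changes from V2 to V5 and V8 due to time alone.
- λ is the verum effect still present 28 days after stopping, and μ is the part still present after 98 days. Placebo has no effect.

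The mean change from V2 to V8 is:
- verum first: d8 + μ
- placebo first: d8 + λ

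A signed rank test on all patients, allocated 1:1, is centred on d8 + (λ + μ)/2. This is non-zero whenever there is drift, even with λ = μ = 0. The sequence contrast is (d8 + λ) − (d8 + μ) = λ − μ. It equals λ only if μ = 0, and it is zero if the effect persists in full (μ = λ).

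**4. Size of the drift problem (illustration).** Inputs are the 86 expected completers (43 per sequence), the planning SD of 3.0 from section 13.3, normal data, no treatment effect and 4000 simulated trials. The drifts are assumed.

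| Common drift | Drift / SD | Signed rank rejects | Rank-sum between sequences rejects |
|---|---|---|---|
| 0 | 0 | 5% | 4% |
| 0.5 | 0.17 | 33% | 5% |
| 1.0 | 0.33 | 86% | 5% |

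The unpaired test keeps its level but loses the precision of the crossover. For a difference of 1.5 with SD 3.0 and 43 per group, power is about 61% (simulated rank-sum) to 64% (normal approximation). 90% would need 85 per group. The 3.0 and 1.5 are planning values for the SARA total score. The protocol gives none for SCAFI, the SARA items, BDI-II or FSS.

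**5. Two possible repairs under the same model.**

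*Post-wash-out change from period baseline:* D1 = V5 − V2, D2 = V8 − V5.
- Verum first: D1 − D2 = (d5 + λ) − (d8 + μ − d5 − λ) = 2·d5 − d8 + 2λ − μ
- Placebo first: D1 − D2 = d5 − (d8 + λ − d5) = 2·d5 − d8 − λ
- Half the difference between sequences: (3λ − μ)/2

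The drift cancels. The result is 0 when λ = μ = 0, λ when the effect persists in full (μ = λ), and 1.5λ when it has gone by 98 days (μ = 0). The test of no persistence is therefore sound. The estimate can be inflated, because V5 as the period-2 baseline carries λ in the verum-first sequence.

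*Change after withdrawal:* V5 − V4 against V8 − V7. With τ the verum effect at week 6, this measures λ − τ, leaving aside what remains of period 1 at V7 and V8. It is zero when the drug does nothing (τ = λ = 0) and also when the effect persists in full (λ = τ), so it cannot tell these apart.

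**The case against.** The strongest case against the point runs as follows.

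- *The data do contain a within-patient contrast.* This is right. V5 and V8 are matched visits, each 28 days off treatment. A reader might infer that no within-patient comparison is possible after treatment, and the documents do not support that. What they lack is a rule that pairs the two visits: V5 is defined only as a baseline, and the visit 8 sentence names visit 8 alone.
- *A comparison of sequences at visit 8 is valid.* This is also right. Sequences are randomised 1:1, so an unpaired comparison is legitimate between patients. It would go too far to call it invalid. It is not the test the sentence names, however, and reading it as the effect of the last treatment assumes that nothing persists 14 weeks after period 1.
- *The SAP can settle it, and the wording is flexible.* The synopsis limits the signed rank test to where it is considered appropriate, and section 13.1 leaves further methodological detail to the SAP. This does not remove the point. Section 13.1 itself names the test, the target and the visit, and no blinded review can create a second visit 8 value.
- *The stakes are low.* This stands, and it limits the weight of the point.
- *The simulation proves little about magnitude.* This stands too. The drifts are assumed and the scale is that of the SARA total score. It shows only which hypothesis the test addresses.

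**Conclusion.** The point holds in a limited form. As written, the visit 8 rule has no verum–placebo pair to work on. Followed literally, it becomes a test of change over time or an unpaired sequence contrast under a paired name. This is an error in a stated rule, not detail left for later.

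Its reach is small. The sentence concerns endpoints that section 13.1 keeps descriptive and outside the hierarchy. The primary analysis, the confirmatory EQ-5D-5L step and the sample size are unaffected.

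Two further inferences are not supported:
- **That all 86 expected completers would supply a V5/V8 pair.** The 86 are patients expected to complete both phases. The protocol gives no figure for attendance at visit 8.
- **That V5−V4 against V8−V7 would answer the persistence question.** It describes change after withdrawal only.

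The algebra assumes additive effects and an inert placebo. The rejection rates assume normal data with SD 3.0 and the drifts shown.

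**What to change.** Replace the visit 8 sentence in section 13.1 with text to this effect:

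> The post-wash-out change from period baseline (V5−V2 after period 1, V8−V5 after period 2) will be compared between verum and placebo within patients who have V2, V5 and V8, allowing for period. The within-patient period differences will be compared between sequences by a rank-sum test. The Hodges-Lehmann shift, halved, estimates the treatment difference. As V5 is also the period-2 baseline, it may carry a persisting period-1 effect, and the estimate will be read with that in mind.

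Add two limits:

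1. Any comparison using visit 8 alone is an unpaired rank-sum test between sequences, labelled a between-sequence description and not a treatment difference.
2. V5−V4 against V8−V7 may be reported only as a description of change after withdrawal, not as a test of persistence.

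State in the results how many patients have all three visits. The cost is a few lines of text, settled before unblinding and carried into the SAP. It needs no new visit, assessment or patient.
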